### Sample size

This is study will be an explorative pilot study. The total sample size required for a two-arm trial following some currently proposed approximation guidelines is between 24 and 70 [21]. Some recently published studies similar to this one have used sample sizes within this range [22–24]. The aim is to recruit 40 participants (*n* = 20 per group). The results of this pilot study will be used to compute sample size and conduct a power calculation to plan a full-scale study.

### Participants

Forty chronic-stage stroke patients with cognitive impairment involving alteration in attention, memory, and/or executive functions will be recruited. The sample will be composed of former patients of Institut Guttmann who have previously received cognitive rehabilitation in the sub-acute phase of evolution.

Recruitment will include postal, email, and telephone contact with participants. Participants will be informed about the study features, goals, and implications of their participation, the duration of the study and the type of procedures that will be applied. Informed consent will be obtained in order to include them in our database. After providing informed consent to participate, participants will schedule an appointment at our center for a baseline testing session.

Inclusion criteria for the trial are (1) age over 18 years old, (2) a stroke diagnosis (ischemic stroke or hemorrhagic stroke); (3) a time of evolution of 12 months or more since stroke occurred (chronic-stage); (4) cognitive impairment confirmed by pre-intervention neuropsychological assessment; and (5) willingness to give written informed consent to participate in the study. Exclusion criteria are (1) diagnosis of language deficits or aphasia; (2) motor impairment concerning upper limbs that may incapacitate them for computer use; (3) severe alteration of the visual field or perceptual problems; (4) health status that may require further intervention or admission to a medical center during the study; (5) neurological or psychiatric history; or (6) substance abuse.

A neuropsychological screen evaluation to check exclusion criteria (1) and (3) will be applied. It will consist of an orientation and language test (orientation, word-repetition, visual-naming, and order comprehension subtests of Test Barcelona-R) [25]. The cutoff needed to participate in the study is 100% proficiency on these tests.

In addition, we will recruit a next-of-kin for each participant, to whom we will administer questionnaires about the impact of attention, memory, and executive function impairment on the patient’s daily life at pre-training, post-training, and follow-up testing stages.

All recruited patients to date are able to consent and understand the implications of the study. Additionally, relatives are involved in both the process of patient consent and patient performance in the study. At the time of recruitment, next-of-kin have been included and informed of the study and its characteristics and implications. This reference next-of-kin collaborates in the study by completing questionnaires about how the participant functions in daily life.

### Ethical considerations and informed consent

Ethics approval has been received from the Care Ethics Committee of Fundació Institut Guttmann and the study will be conducted in accordance with the Declaration of Helsinki [26]. A neuropsychologist will explain the study to each participant by phone and in person. An information letter will be given to participants. Participants will be free to ask any question about study treatments and under no circumstances will study professionals imply that certain cognitive results will occur as a result of study participation. Further, a participant may resign from the study at any time.

The protocol follows the recommendations of the Standard Protocol Items: Recommendations for Interventional Trials Statement (SPIRIT) 2013 [27] (Additional files 1 and 2).

### Setting

The study requires that five neuropsychological assessments be held in a hospital setting at the Institut Guttmann. The Institut Guttmann is a hospital and academic institution located in Badalona (Barcelona, Spain). The hospital is specialized in the medical and surgical treatment and comprehensive rehabilitation of people with spinal cord injury, acquired brain injury, or other neurological disabilities. The institute’s main objective is to provide specialized, comprehensive, continuous, and personalized care, incorporating the highest levels of science and technology. In the case of patients with acquired brain injury, part of the rehabilitation includes cognitive rehabilitation, which is performed by neuropsychologists.

Participants will perform home-based interventions (GNPT^®^ and ictus.online).

### Intervention

#### Experimental intervention

GNPT^®^ is a tele-rehabilitation platform that allows therapists to configure and schedule rehabilitation sessions, consisting of a set of personalized computerized cognitive exercises. The examiner from the study will perform the initial neuropsychological assessment and the results of this assessment will be stored in the GNPT^®^ system by a study researcher. The program will then calculate a cognitive profile using these results, taking into account the patient’s age and educational level. Using this profile, the program will assign a set of computerized tasks to a certain day, configuring the input parameters of each task in order to personalize treatments. The neuropsychological assessment done at A1 (for group A) and A3 (for group B) will be used to establish the cognitive profile. Starting from each patient’s initial cognitive capacity, therapeutic plans will be adjusted to the level of execution and adapted to the patient’s evolution according to the obtained results. The adjustment is performed by GNPT^®^ using an automated process. The difficulty level of the tasks will vary and will be adapted according to the participant’s performance. Once a rehabilitation session is defined, the participant executes the assigned tasks, sending the results back to the server located at Institut Guttmann, such that therapists can asynchronously see the performance. A researcher from the study group will be exclusively dedicated to supervising this process.

The treatment consists of a set of 1-h sessions, five sessions per week during 6 weeks. A series of cognitive exercises of attention, memory, and executive functions will be conducted in each session (Fig. 3).

**Fig. 3 Fig3:**
[figure not shown]
Experimental intervention (GNPT^®^) screenshots. **a** To access to the platform, the user must enter their username and password. **b** Each exercise begins with an instruction screen. **c** Example of a cognitive rehabilitation exercise. **d** At the end of each exercise, a results screen is displayed

### Sham intervention

For the sham intervention, a web platform has been developed and is available online through a the domain ictus.online (Fig. 4). This web platform has a graphic interface design similar to GNPT^®^. After login, it allows participants to access a daily session, which presents four videos of 10 minutes each. After each video, the participant must complete a three-question quiz about the contents of the video (for example, “What animal appears in the video?”). This makes each session last approximately 1 hour in total. The difficulty level of the questions is minimal and independent of the results of the neuropsychological assessment and will remain stable regardless of the execution of the participants. The quality of execution of this condition will be monitored.

**Fig. 4 Fig4:**
[figure not shown]
Sham intervention (ictus.online) screenshots. **a** To access to the platform, the user must enter their username and password. **b** Each exercise begins with an instruction screen. **c** The user watches a 10-min video. **d** When finished, the user accesses a three-question quiz with four response options. **e** When the quiz is finished, a results screen is displayed. In each session, three videos with their corresponding quiz are presented

Both the experimental intervention group and the sham intervention group will receive a username and password for logging in.

As adherence strategies, the organizers will offer flexible schedules to perform the exercises, phone calls to confirm appointment dates, and periodic progress reports to keep participants informed on their personal progress in the study (i.e., how much work they have completed, how much longer the study will last, etc.). Additionally, connection frequency will be supervised. To reduce risk, a member of the organizing team will contact the participants if they do not perform any exercise at any of the platforms of treatment for 3 consecutive days (GNPT^®^ or ictus.online) and will reinforce treatment compliance. Attrition will be considered when (1) presence of a new neurological condition appears during the study, or (2) loss of contact with participants occurs during the study and follow-up.

### Measures

Demographic information (age, sex, marital status, occupation, education level) and injury history (time of evolution, type of stroke) from all participants will be collected. Whether they have received or are currently receiving any kind of neuropsychological or functional rehabilitation at the moment of joining the study will be also recorded. The information collection method will be a personal interview. A comprehensive neuropsychological battery will be used to assess the participants. This battery is comprised of performance-based measures to assess attention (Conners Continuous Performance, CPT-II) [28], Trail Making Test A and B [29]), memory (Digit Span forward from the Wechsler Adult Intelligence Scale (WAIS-III) [30], Rey Auditory Verbal Learning Test [31]), speed of processing (Digit Symbol-Coding test from WAIS-III), visuoconstruction (Block Design test from WAIS-III), and executive functions (Digit Span backwards and Letter-Number Sequencing from WAIS-III, Stroop Color and Word test [32], Wisconsin Card Sorting Test – computerized version [33], and a Spanish phonemic fluency test – PMR [34]). Administered rating measures (Rating Scale for Attentional Behavior (RSAB) [35]; Prospective and Retrospective Memory Questionnaire (PRMQ) [36]; Behavior Rating Inventory of Executive Function – Adult Version (BRIEF-A)) [37] will be administered alongside the performance-based measures. All these rating measures will be applied to the patient (self-report) and their recruited next-of-kin (informant-report). Finally, a psychological well-being self-rating scale (Hospital Anxiety and Depression Scale [38]), Patient Competency Rating Scale [39], and the Community Integration Questionnaire [40] will be administered. The Hospital Anxiety and Depression scale will be used to detect participants with emotional disorders. The Patient Competency Rating Scale comprises 30 items, spanning a range of everyday situations and behaviors, and for each item, the patient must make judgment about their own level of competency. The Community Integration Questionnaire is a self-rating scale developed to measure community integration that comprises three subscales (home integration, social integration, and productive activities). These rating measures have been used before in other studies involving stroke patients [41–43].

#### Primary outcome measures

The primary outcome measures are performance-based measures and rating measures of attention, memory, and executive functions. Since they are different cognitive domains, we need to use different measures for attention (two primary outcomes: the CPT-II and RSAB), memory (Rey Auditory Verbal Learning Test, Digit Span forward from WAIS-III, and the PRMQ), and executive functions (Spanish phonemic fluency test – PMR, Digit Span backward, and the Letter-Number Sequencing Subtests from the WAIS-III and the BRIEF-A). CPT-II is a task-oriented computerized assessment of sustained attention; the Rey Auditory Verbal Learning Test assesses short- and long-term verbal memory and recognition; the PMR test assesses capacity of word generation according to an initial letter (P, M and R); the Digit Span forward test measures the span of immediate verbal recall; Digit Span backward and Letter Number assess working memory; and the RSAB comprises 14 items aimed to identify attentional difficulties on daily routines. The PRMQ includes 16 items, and was designed to evaluate prospective and retrospective memory in the short and long term. The BRIEF-A is designed to assess executive function behaviors on day-to-day activities.

In order to reduce the number of analyses, we will create composite cognitive indices – one for attention, another for memory, and another for executive functions, using sub-scores from the various performance-based measurements of the primary outcome. Composite cognitive indices will include sub-scores on CPT-II, namely number of omissions, number of commissions, and hit of response for attention; sub-scores on Rey Auditory Verbal Learning Test (Trials 1–5 recall, long-delay free recall and recognition) and Digit Span forward from WAIS-III (immediate recall of a series of numbers) for memory; and scores on Spanish phonemic fluency test – PMR (phonemic word fluency), Digit Span backward from the WAIS-III (immediate recall of a sequence of numbers in reverse order in which it was presented), and Letter-Number Sequencing Subtests from the WAIS-III (recall of progressively longer lists of intermixed letters and numbers in alphabetical and then numerical order) for executive functions.

#### Secondary outcome measures

Secondary outcomes are the Digit Symbol-Coding and the Block Design Subtests from the WAIS-III, Trail Making Test A and B (TMT-A and TMT-B), Wisconsin Card Sorting Test, and Stroop Color and Word Test. The Digit Symbol-Coding assesses the speed of processing; Block Design evaluates visuoconstruction and planning; TMT-A measures visual attention, while TMT-B measures task-switching; the Wisconsin Card Sorting Test is a measure of cognitive flexibility; and the Stroop Color and Word test is used as a measure of inhibitory control.

#### Statistical analysis

##### Analysis

Data analysis will be based on the intention-to-treat principle, which means that all participants who were randomized will be included in the final analysis, regardless of their adherence to any of the interventions. To avoid the problems derived from missing data (no attendance to neuropsychological assessments), blank spots will be filled with missing data imputation technique last value carried forward.

In order to detect changes in the variables recorded for the primary outcome and secondary outcome, a within-subject comparison pre-/post-intervention in both groups after both interventions will be made, as well as comparisons between groups (group A and group B).

Our null hypothesis is that a difference between baseline scores (A1 for group A and A3 for group B) and scores post-treatment (A2 for group A and A4 for group B) will not be significantly different from zero. Therefore, the Kolmogorov–Smirnov test will be used to examine the data for normality, and either ANOVA (parametric test) or Kruskal–Wallis (non-parametric test) will be used to analyze the measurements. A significance level of 95% will be used (*P* < 0.05 cutoff). Demographic (age, sex, years of education) and etiologic characteristics (ischemic stroke or hemorrhage) will be described using descriptive statistics for each group (group A and group B). The Bonferroni method will be applied to adjust the overall level of significance for multiple outcomes.

Alternatively, composite indices will be created by transforming raw neuropsychological test scores into z scores using published normative data. Domains will be created by averaging the z scores for each test within the domain (M = 0; SD = 1). This system has been used before in similar studies [44, 45].

If the sample size of this pilot study allows, a longitudinal mixed model will be applied.

Data analysis will be performed by an analyst outside the study with the statistical analysis software R and appropriate packages (“lmm” and “psych”) [46].

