**Fig. 2 Fig2:**
[figure not shown]
SPIRIT figure: schedule of enrolment, interventions and assessments

Evaluations will be conducted pre- and post-training by the study examiner. The examiner will be blind to the allocation of participants. Pre-testing will occur immediately before starting training (A1), and post-testing will occur immediately following both experimental and sham interventions (A2/A4) and after the 3-month washout period (A3). A follow-up neuropsychological assessment will be performed 6 months after treatment has terminated (A5).

A study researcher blinded to assessment procedure will perform the randomization of participants using the rand() function of Microsoft Excel software (Microsoft Excel 2010 for Windows), which is considered a good tool of randomization, having passed the Diehard test [20]. Each participant will have a “list entry” in our database, meaning that they will be stratified based on the two variables of interest in our study – sex (male or female) and type of stroke (ischemic or hemorrhagic). The rand() function will then assign random numbers from 0 to 1 to the stratified sample. The random numbers are ordered from lowest to highest and the first half of the list is assigned to group A and the second half to group B. A study researcher will create a letter with the information of the intervention to be performed (GNPT^®^ or ictus.online) for each participant and will place it in a sealed envelope. The examiner will deliver the sealed envelope to each participant when the first and the third neuropsychological examinations (A1 and A3) take place.

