## Discussion

The first objective of this research is to study the effectiveness of a patient-customized computerized cognitive training program (GNPT^®^) as a home-based cognitive stimulation tool for stroke patients in the chronic stage of recovery. We hypothesize that training cognitive functions of attention, memory, and executive functions with GNPT^®^ could lead to better function of those cognitive domains post-therapy. Furthermore, we want to study whether customized cognitive training could lead to an improvement in other contexts different from the examination tests, improving performance in both related (near transfer) and unrelated (far transfer) tasks. Finally, we want to study the impact of variables such as demography and etiology on rehabilitation outcome.

The strengths of our study include that it is designed to (1) be easily replicated in new patient cohorts, (2) minimize unintended variability by reducing intervention heterogeneity, (3) adjust the type and difficulty of exercises to the specific cognitive impairment profile of patients, and (4) monitor adherence and performance of each exercise during the whole treatment.

Furthermore, our study focuses on targeting cognitive rehabilitation toward the improvement of the quality of life of the patient. In this sense, we include in our primary outcome measures an assessment of functioning in daily life, before, during, and after the performance of both interventions. Additionally, our design is longitudinal, which offers the possibility of studying the maintenance of the results over time (over 3 and 6 months). The timing of the primary outcome is 3 months. The purpose of the follow-up at 6 months is to check the evolution of patients once they have stopped receiving any type of intervention.

Furthermore, the execution of both interventions will be remotely monitored and we will be able to record the quantity and quality of the execution of the participants. Nevertheless, we consider a limitation the fact that we will not be able to control the environmental conditions in which participants perform the tasks. Another limitation is that the battery assessment will be the same throughout the study, which might create a learning effect and/or ceiling effect in some evaluation tasks.

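### Filling missed assessments by last value carried forward pulls change scores towards zero, understates their variance and gives unreliable inputs for sizing the full-scale trial

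*Protocol article*

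**What the plan says.** The Analysis subsection commits to intention-to-treat: "all participants who were randomized will be included in the final analysis, regardless of their adherence to any of the interventions". Its one rule for missed visits is that "blank spots will be filled with missing data imputation technique last value carried forward". It names no other method and no sensitivity analysis for missing data. A longitudinal mixed model is mentioned, but only on condition that the sample is large enough, and not in place of the carried-forward values.

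The visits the rule acts on are set out under Design: A1 before training, A2 and A4 straight after each intervention, A3 after the 3-month washout, and A5 six months after treatment ends. The null hypothesis concerns the difference between "baseline scores (A1 for group A and A3 for group B) and scores post-treatment (A2 for group A and A4 for group B"). The plan also compares pre- and post-intervention scores within both groups for both interventions.

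Two uses of the results matter here. The Sample size section says: "The results of this pilot study will be used to compute sample size and conduct a power calculation". The Discussion counts it as a strength that the longitudinal design "offers the possibility of studying the maintenance of the results over time (over 3 and 6 months").

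**The concern.** Carrying the last value forward assumes that a person's score would not have moved. The article itself gives reasons to expect movement: the intervention is meant to improve scores, a washout separates the periods, and the Discussion warns of a learning effect because the same battery is repeated. Unchanged is therefore not a neutral guess. The Intervention section also counts a new neurological condition as attrition. In that case the rule would record cognition as it was before the event.

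The crossover makes this worse, because a value can be carried from one treatment period into the next. The effect depends on the visit missed:

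- **A2 or A4 missed (with or without the visit before it):** the post-treatment score equals the score before it, so the change is exactly zero.
- **Only A3 missed:** A2, taken immediately after the first intervention, becomes the period-2 baseline. The change becomes A4 minus A2, which is distorted but not zero.
- **A5 missed:** A4 is copied and that person's loss after treatment is zero.

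At stake are the estimated training gain, the picture at follow-up, and the effect and variance estimates that the pilot is meant to supply.

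**Working it through.** **The plan's own figure.** 2 x 20 = 40 participants, inside the cited range of 24 to 70. It does not come from a power formula, and no attrition rate, effect size, SD or visit correlation is stated. Everything below therefore uses assumed inputs.

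**Formula.** Let a share p of participants have an imputed change of 0, and let the others have mean change d and SD of change s. Then

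- mean = (1 - p) d
- variance = (1 - p) s² + p(1 - p) d²

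**Group B's GNPT change (A3 to A4).** Assume d = 0.50 outcome SD and a retest correlation of 0.75, so s = sqrt(2 x 0.25) = 0.707 and s² = 0.5. At p = 0.2:

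- mean = 0.8 x 0.50 = 0.40
- variance = 0.8 x 0.5 + 0.16 x 0.25 = 0.44, a ratio of 0.44/0.5 = 0.88, or 12% too low

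A simulation with 20 per group, A3 and A4 both missing at random, gave mean changes of 0.449, 0.405 and 0.349 at 10, 20 and 30% missing, against a true 0.50.

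**Only A3 missed, group A.** Assume a GNPT gain of 0.50, half of it lost over washout, and no sham effect. The true sham change is 0, but those with A3 missing show 0.25 - 0.50 = -0.25. At 20% missing the group mean becomes 0.2 x (-0.25) = -0.05.

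**A5 missed.** With a true mean decline from A4 to A5 of -0.25 and 20% missing, the result is 0.8 x (-0.25) = -0.20.

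**Which SD shrinks.** In a five-visit simulation (correlation 0.7, 20% missing), the SD of period-2 change in group B fell from about 0.775 to 0.722 when A4 was missed. The SD of the scores at A4 itself stayed at about 1.00 to 1.02. From the formula, the variance of change falls whenever (1 - p)(1 + p d²/s²) < 1, that is, when d/s < 1/sqrt(1 - p). That limit is 1.12 at p = 0.2 and 1.20 at p = 0.3. The illustration has d/s = 0.50/0.707 = 0.71, well below it.

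**Planning the next trial.** Here the scale is the SD of change: true s = 1, true difference 0.5, two-sided 0.05, 80% power, no change in the control arm, and the active-arm variance used for both arms. With n per arm = 2(1.96 + 0.8416)² s²/d², the undistorted answer is 2 x 7.849/0.25 = 62.8, so 63. At p = 0.2 the variance is 0.8 + 0.16 x 0.25 = 0.84. Then 62.8 x 0.84 = 52.7 gives 53 per arm if the target difference comes from outside, and 52.7/0.8² = 82.4 gives 83 if the diluted pilot effect is used too.

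| Imputed | Mean change (true 0.50) | Variance ratio (s = 0.707) | SD of change (true 1) | n per arm, shrunken SD and external difference | True power at that n | n per arm, shrunken SD and diluted effect |
|---|---|---|---|---|---|---|
| 10% | 0.45 | 0.945 | 0.960 | 58 | 76.8% | 72 |
| 20% | 0.40 | 0.880 | 0.917 | 53 | 73.0% | 83 |
| 30% | 0.35 | 0.805 | 0.867 | 48 | 68.8% | 97 |

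**The case against.** **The shift is small beside the noise.** This is partly right. In a simulated crossover estimate combining both periods (true effect 0.40, correlation 0.75, 20 per group), carrying values forward gave 0.364 at 20% missing. The standard error of that estimate is about sqrt((1/20 + 1/20)/4) = 0.158, so the shift is 0.036/0.158, about a quarter of a standard error, and towards no effect. The article does not specify that combined estimate, however. On group B's own pre-post change, which it does specify, the standard error is 0.707/sqrt(20) = 0.158 and the shift is 0.10, about 0.6 of a standard error.

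**The benchmark assumes dropouts would have had the full gain.** This stands in part. Someone who leaves before period 2 may never start GNPT, and a missing-at-random model gives that person the expected gain of those who stayed. Some of the drop from 0.50 to 0.40 is thus a difference in the question asked, not proven bias. It does not rescue the rule, which also sets practice and washout change to zero and treats the guess as data. It does justify a sensitivity analysis.

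**A mixed model is already foreseen.** It is conditional, and nothing says it would use unfilled data. Fitted to filled data, it would inherit the same distortion.

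**This is an exploratory pilot.** True, and it tempers the weight of any single test. But supplying planning estimates is the pilot's declared use, and those are what the rule distorts.

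**Conclusion.** The point holds. As written, the rule pulls mean change towards zero for anyone missing A2 or A4, with later dropout falling mainly on group B's GNPT contrast. It replaces the washed-out baseline when only A3 is missed, softens the average decline when A5 is missed, and understates the variance of within-person change provided the mean change is less than about one SD of change. At 20% missing the illustrations are 0.50 to 0.40, -0.25 to -0.20, and a 12% lower variance. They rest on assumed attrition, effect and correlation; the mechanism follows from the stated rule and visit schedule.

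Four stronger readings are tempting but unsupported:

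- **Every missed period-2 visit forces zero change.** That requires a missed A4; a missed A3 alone does not do it.
- **The rule creates maintenance.** It attenuates an average decline. Maintenance is mentioned as a possibility in the Discussion, and the Analysis subsection specifies no A5 test.
- **All SDs shrink.** The SD at a single visit is roughly unchanged.
- **The full-scale trial will be too small.** The Sample size section does not say which pilot estimates will be used, and the error reverses (83 against 63 per arm at 20%) if the diluted effect is used as well. Mis-sized is as far as the document allows.

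**What to change.** In the Analysis subsection, replace the last-value-carried-forward sentence with a likelihood-based mixed model, valid under missing at random, fitted to all observed assessments of all randomised participants. Make it the main analysis without the sample-size condition, and carry no value between any two visits. Five visits from 40 people give up to 5 x 40 = 200 records per outcome, so the model should be kept simple. Everyone with at least one score stays in, which preserves the intention-to-treat aim.

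State in the Sample size section that effect and variance estimates for the full-scale trial will come from observed or model-based data.

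Add one simple sensitivity analysis for data not missing at random, for example multiple imputation in which people who leave before or during GNPT are given less than the completers' gain.

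The cost is a few sentences, one extra analysis and slightly wider confidence intervals. Data collection does not change.

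### Bonferroni is scoped to outcomes only, while each outcome gets four pre/post comparisons plus an unstated number of between-group comparisons, none named as deciding

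*Protocol article*

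**What the plan says.** All of the relevant text is in the Analysis section of the protocol article, except the outcome list.

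- **Comparisons.** The section opens with "In order to detect changes in the variables recorded for the primary outcome and secondary outcome" and then plans "a within-subject comparison pre-/post-intervention in both groups after both interventions will be made, as well as comparisons between groups (group A and group B"). Two groups times two interventions makes four pre/post comparisons per outcome. The between-group comparisons are in the plural but not counted.
- **Stated hypothesis.** "Our null hypothesis is that a difference between baseline scores (A1 for group A and A3 for group B") and the matching post-treatment scores (A2 and A4) does not differ from zero. This is the pre/post change under GNPT in each group. Sham does not enter it.
- **Tests.** After a normality check, "either ANOVA (parametric test) or Kruskal–Wallis (non-parametric test) will be used to analyze the measurements". Whether this means one overall test per outcome or separate contrasts is not said.
- **Cutoff.** One threshold is given for all comparisons: "A significance level of 95% will be used (*P* < 0.05 cutoff").
- **Multiplicity.** "The Bonferroni method will be applied to adjust the overall level of significance for multiple outcomes". No divisor is given, and contrasts are not mentioned.
- **Outcomes.** Primary outcome measures lists measures by domain, beginning with attention ("two primary outcomes: the CPT-II and RSAB"), and adds: "In order to reduce the number of analyses, we will create composite cognitive indices".

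**The concern.** Dividing alpha by the number of outcomes holds the overall level only when each outcome carries one test. Here each outcome carries at least four, and the plan neither ranks them nor sets any aside as descriptive.

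Two things follow. First, a result could be reported as significant after Bonferroni although the correction did not count the tests from which it was picked. Second, the comparisons can disagree. Group A may improve under GNPT while the period 1 group comparison shows nothing, or the two groups may differ in one period and not in the other. Apart from the stated null, which leaves out the sham condition, nothing in the article says which result answers the question of benefit.

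**Working it through.** **Inputs from the protocol article**

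- Cutoff 0.05 (Analysis); two-sided is assumed, since sidedness is not stated.
- 20 patients per group (Sample size).
- Number of outcomes m: 3 composite indices; or 9 primary measures (attention 2, memory 3, executive functions 4); or 15 with the 6 secondary measures, counting Trail Making A and B separately.
- Contrasts per outcome k: 4 are explicit. 4 + 2 = 6 if the groups are compared once in each period, which is an inference.

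**Assumed, not in the article:** within-person correlation 0.7 between visits; between-outcome correlation r from 0 to 0.9; no treatment effect and no practice effect.

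**Step 1: the plan's rule with one test per outcome.** The sum of the levels is m × 0.05/m = 0.05. If the tests are independent, 1 − (1 − 0.05/m)^m gives 0.0492 for m = 3 and 0.0489 for m = 9 and m = 15. The rule does what it should in this case.

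**Step 2: k tests per outcome, all independent.** The formula becomes 1 − (1 − 0.05/m)^(k·m), with upper bound k × 0.05.

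| k | m = 3 | m = 9 | m = 15 | Upper bound |
|---|---|---|---|---|
| 4 | 0.183 | 0.182 | 0.182 | 0.20 |
| 6 | 0.261 | 0.260 | 0.260 | 0.30 |

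**Step 3: allowing for dependence.** The two between-group differences in change are linear combinations of the four within-group changes, and outcomes are correlated, so independence overstates the rate. A simulation (20,000 replicates per setting) used four paired t-tests on change and two two-sample t-tests on change, each at 0.05/m. The table gives the chance of at least one false positive.

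| m | r | Stated null, each group separately | Four pre/post contrasts | Four plus two between-group |
|---|---|---|---|---|
| 3 | 0 | 0.094 | 0.183 | 0.224 |
| 3 | 0.5 | 0.090 | 0.168 | 0.205 |
| 3 | 0.9 | 0.064 | 0.122 | 0.147 |
| 9 | 0 | 0.095 | 0.181 | 0.230 |
| 9 | 0.5 | 0.083 | 0.156 | 0.193 |
| 9 | 0.9 | 0.037 | 0.072 | 0.090 |
| 15 | 0 | 0.096 | 0.183 | 0.234 |
| 15 | 0.5 | 0.077 | 0.147 | 0.185 |
| 15 | 0.9 | 0.031 | 0.058 | 0.073 |

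The four explicit contrasts run from 0.058 to 0.183. With two between-group contrasts added, the range is 0.073 to 0.234, quoted as 7 to 24% to allow for simulation error at the top.

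**Step 4: the stated null alone.** Pooled over the two groups it is one test per outcome, so Step 1 applies and the rate is at most about 5%. Tested in each group it is two tests per outcome, simulated at 3 to 10%.

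**Step 5: one GNPT-minus-sham contrast.** This too is one test per outcome, so the bound is again m × 0.05/m = 5%. Let the GNPT-minus-sham effect be τ and the practice changes in the two periods be p1 and p2, the same in both groups. The within-patient difference (GNPT change minus sham change) then has expectation τ + p1 − p2 in group A and τ + p2 − p1 in group B. Their average is τ, so practice cancels. In a pre/post contrast it does not.

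**The case against.** The strongest case on the other side has five parts.

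1. **The number of tests is not fixed.** A reader might infer at least six contrasts per outcome. The text supports four; the between-group count is open, so six is only one reading.
2. **Separate tests are assumed.** The article names ANOVA or Kruskal–Wallis, and a longitudinal mixed model if the sample size allows. One overall test per outcome would not produce these rates. That is fair, and the figures are conditional on separate testing. But the ANOVA is not described as a single overall test, the mixed model is conditional, and Kruskal–Wallis compares independent groups, so it cannot serve as one test over repeated assessments.
3. **A null hypothesis is stated.** If it alone is confirmatory, the excess disappears (pooled) or shrinks to at most about 10% (by group). This stands as arithmetic. The article does not say that the other comparisons are descriptive, nor that the groups are pooled.
4. **Five per cent over everything is not promised.** A reader might infer that the true rate is 12 to 22% instead of a stated 5%. The documents do not support that. The Bonferroni sentence is tied to outcomes, and that range rests on assumed correlations. It also counts the two sham pre/post contrasts, which cannot be claimed as GNPT benefit. For the four contrasts that could be so claimed (GNPT pre/post in each group and the group comparison in each period), the simulated rate is 8 to 16% for 3 or 9 outcomes and r from 0 to 0.8.
5. **It is an exploratory pilot, and an analysis plan may hold the detail.** The first lowers the severity. The second would excuse silence, but here the article does fix a rule, and its scope does not match the comparisons listed beside it.

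**Conclusion.** The concern holds in a limited form. The multiplicity rule covers outcomes but not the several comparisons planned within each outcome, and no comparison is named as deciding. Tested separately at 0.05 divided by the number of outcomes, the comparisons do not keep the overall rate at 5%; the excess is as computed in Step 3.

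Those figures depend on separate testing and on correlations that the article does not give. They also assume no practice effect, so they measure multiplicity alone. The Discussion concedes a possible learning effect from repeating the same battery. Such an effect could make pre/post comparisons significant without any GNPT benefit, and no division of alpha would correct that.

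Severity is low to moderate. The trial is an exploratory pilot meant to inform a full-scale study, but it chose significance testing with a correction, and readers will take a corrected result as controlled.

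**What to change.** Add two sentences to the Analysis section:

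1. For each primary outcome, the deciding contrast is the GNPT-minus-sham difference in pre/post change, estimated from both periods, and the Bonferroni correction across outcomes applies to that contrast.
2. The within-group pre/post comparisons and the period-by-period group comparisons are descriptive, reported as estimates with confidence intervals and without significance claims.

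Dividing alpha by outcomes times contrasts is not a good substitute, because it keeps pre/post tests that practice alone can make significant.

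No new data are needed, since A1 to A4 already supply the contrast. The cost is that within-group p-values can no longer be presented as significant findings. The two-period contrast also relies on first-period effects not carrying into second-period change; the descriptive period-by-period estimates let a reader judge that.
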